## Abstract

**Background:**

Children hospitalised with severe acute malnutrition (SAM) are frequently complicated (>50%) by diarrhoea ( ≥3 watery stools/day) which is accompanied by poor outcomes. Rehydration guidelines for SAM are exceptionally conservative and controversial, based upon expert opinion. The guidelines only permit use of intravenous fluids for cases with advanced shock and exclusive use of low sodium intravenous and oral rehydration solutions (ORS) for fear of fluid and/or sodium overload. Children managed in accordance to these guidelines have a very high mortality. The proposed GASTROSAM trial will reappraise current recommendations with mortality as the primary outcome. We hypothesize that liberal rehydration strategies for both intravenous and oral rehydration in SAM children with diarrhoea may reduce adverse outcomes.

**Methods:**

An open Phase II trial, with a partial factorial design, enrolling children in Uganda, Kenya, Nigeria and Niger aged 6 months to 12 years with SAM hospitalised with gastroenteritis (>3 loose stools/day) and signs of moderate and severe dehydration. In Stratum A (severe dehydration) children will be randomised (1:1:2) to WHO plan C (100mls/kg Ringers Lactate (RL) with intravenous rehydration (IV) given over 3-6 hours according to age including boluses for shock), slow rehydration (100 mls/kg RL over 8 hours (no boluses)) or WHO SAM rehydration regime (ORS only (boluses for shock (standard of care)). Stratum B incorporates all children with moderate dehydration and severe dehydration post-intravenous rehydration and compares (1:1 ratio) standard WHO ORS given for non-SAM (experimental) versus WHO SAM-recommended low-sodium ReSoMal. The primary outcome for intravenous rehydration is mortality to 96 hours and for oral rehydration a change in sodium levels at 24 hours post-randomisation. Secondary outcomes include measures assessing safety (evidence of pulmonary oedema or heart failure); change in sodium from post-iv levels for those in Stratum A; perturbations of electrolyte abnormalities (severe hyponatraemia <125 mmols/L or hypokalaemia.

**Discussion:**

If the trial shows that rehydration strategies for non-malnourished children are safe and improve mortality in SAM this could prompt revisions to the current treatment recommendations or may prompt future Phase III trials.

## Introduction

Annually, there is estimated to be 2.5 billion cases of acute gastroenteritis in children less than under five years of age. Gastroenteritis is reported to be the second largest cause of mortality in this age group and most deaths occur in low resource settings such as sub-Saharan Africa
^
1
^. A large case-control study Global Enteric Multicentre study (GEMS) conducted in Africa and Asia, examining the pathogenic aetiology and outcome of children admitted to hospital with moderate to severe gastroenteritis, found that they are 8.5 times more likely to die than children admitted without gastroenteritis (controls)
^
2
^. Thirty percent of the fatalities occurred less than seven days following hospitalisation and that baseline nutritional status an important factor in outcome. Improvements in early management may therefore be critical for improving outcome.

For children with severe acute malnutrition (SAM) the current World Health Organization (WHO) recommendations for rehydration of children with signs of severe dehydration and diarrhoea are exceptionally conservative and somewhat controversial
^
3
^. First, recommendations for intravenous rehydration are restricted only to those with advanced shock, a group we have documented to have an exceptionally high mortality rate (82% Day 28 mortality) on current guidelines since the guidelines focus on the exclusive use of oral rehydration using low-sodium oral rehydration solutions (ORS) (ReSoMal)
^
4
^. The guidelines lack relevant clinical studies, founded largely on a time-honoured and strongly held belief that the malnourished heart is at risk of heart failure. Moreover, guidelines indicate SAM children have an inability to cope with sodium-rich solutions (expert opinion, with no published primary data) and recommend a preference of hypotonic (half-strength Darrow’s or lactated Ringers with additional 5% dextrose) solutions for intravenous resuscitation
^
5
^. The controversy surrounding these recommendations was reviewed by [name] in 2006 (in a critical appraisal of the management of severe malnutrition) in which he states “The World Health Organization (WHO) manual has five pages on this issue (rehydration), which is somewhat unbalanced compared with the 11 lines on TB/HIV”
^
3
^. This is rather paradoxical since these were published there have been few studies to inform such recommendations, and the limited number of studies and trials suggesting that standard approaches are not harmful were not included in the WHO recommendations. Subsequent updates of these recommendations have also failed to include references to relevant research challenging these guidelines which we now review. 

### Challenging the WHO recommendations

First, these recommendations for rehydration and shock management are not physiological, since isotonic solutions are required to expand circulating volume, with hypotonic solutions more liable to cause water overload. Secondly, there are few commercially available preparations of half-strength Darrow’s or lactated Ringers with additional 5% dextrose (which the guidelines recognize)
^
6
^, but there is ready availability of half-strength Darrow’s and 50% dextrose. Reconstitution at the bedside is recommended but this risks contamination (infection) and medication errors (inaccurate glucose dosage calculation). Moreover, the recommendation that the reconstituted fluid should be used immediately is difficult to adhere in ordinary care. There is also a similar issue with the availability of low sodium rehydration solution (ReSoMal) which is frequently not stocked in resource limited hospitals as the sole producer of ReSoMal is Nutriset, France. Thus, as ReSoMal is infrequently available, even the oral rehydration aspect of these recommendations is impossible to implement. Finally, the views that ‘severe diarrhoea’ is unusual in SAM and the presence of diarrhoea is usual but of trivial consequence is not supported by scientific evidence
^
7
^. Furthrmore, guidelines indicating that signs of severe dehydration (decreased skin turgor or sunken eyes) are unreliable and reflect a lack of fat mass
^
8
^ lack a scientific published evidence-base and are at odds with published data
^
7
^. In two decades, guidelines have not been revised (including updated 2013 guidelines)
^
5
^ despite emerging evidence from Africa challenging these premises, where both diarrhoea and signs of severe dehydration were shown to have very high mortality rates
^
7,
9
^. These are summarised below.

### Data from Africa and systematic reviews

A prospective study involving 920 Kenyan children showed that 50% of children admitted with SAM had diarrhoea (case-fatality 21% versus 9% without diarrhoea) and a further 16% developed diarrhoea during admission (case-fatality 18%)
^
7
^. Key risk factors for death were bacteraemia and signs of severe dehydration (decreased skin turgor or sunken eyes)
^
7
^, and severe hyponatraemia - challenging the assumption that signs of severe dehydration are ‘unreliable’ and diarrhoea plays a limited role in the poor outcomes.

We have recently conducted two systematic reviews of randomized trials and observational studies in children with SAM and gastroenteritis with dehydration summarizing the evidence underpinning the intravenous and oral rehydration recommendations for SAM
^
10,
11
^

The intravenous rehydration review identified four studies which included 883 children, all of which were conducted in low resource settings
^
10
^. Two were randomised controlled trials
^
12,
13
^ and two observational cohort studies
^
14,
15
^. There was no evidence of fluid overload or other fluid-related adverse events including children managed on more liberal rehydration protocols. Mortality was high overall, particularly in children with shock managed on WHO recommendations (Day-28 mortality 82%). There was no difference in safety outcomes when different rates of intravenous rehydration were compared.

The Appropriate Fluid Resuscitation In Malnutrition (AFRIM) study incorporated systematic and detailed assessment of myocardial function demonstrating evidence of fluid responsive myocardial indices and that median systematic vascular resistance index remained very high post fluid resuscitation indicative of ‘under filling’ rather than overload
^
15
^. Another clinical study examining myocardial function in Kenyan children (CArdiac Physiology in MALnutrition [CAPMAL]) concluded that although cardiac mass is reduced (consistent with body mass) there were no significant differences in cardiac index, stroke volume index, and heart rate between inpatient children with and without SAM
^
16
^. This was also the conclusion of another larger study in Malawian children with severe malnutrition
^
17
^. 

For the management of ‘some dehydration’ the systematic review of oral rehydration
^
11
^ identified only two small clinical trials conducted in Asian children which have compared the use of ReSoMal against other low osmolar ORS
^
18,
19
^; both were equally effective in rehydration. However, both trials showed the development of hyponatraemia with ReSoMal, with one child developing seizures with severe hyponatraemia. Neither reported any mortality. No trials have been conducted in Africa, where SAM mortality remains high, with hyponatraemia as a key risk factor for mortality
^
7
^.

Finally, relevant to a broader population hospitalised with acute diarrhoea with severe dehydration (
^~^10% weight loss) a prospective study showed that ~20% temporarily fulfilled anthropometric criteria for SAM (mid-upper arm circumference (MUAC) <11.5cm) but were ‘reclassified’ as undernourished
^
20
^ following rehydration. Thus, the current recommendations have much wider implications as potentially 20% of non-SAM children could be inappropriately rehydrated in accordance with the WHO SAM guideline. This may have contributed to the poor outcomes observed in the GEMS study
^
2
^.

## Protocol

Trial Registration
ISRCTN76149273 (registered on 8 August 2018)

Protocol Version 3.0 Date 25
^th^ November 2022

### Justification for the study

The principal aim of GASTROSAM is to reappraise these recommendations and evaluate more liberal strategies for both intravenous and oral rehydration (since they are interlinked as a ‘treatment bundle’). Demonstrating that intravenous rehydration is safe in children with SAM will be an important achievement.

Outcome remains poor in children hospitalised with diarrhoea, especially those with moderate and severe malnutrition. There is an urgent need to reappraise both the rehydration guidelines for both SAM and non-SAM patients owing to the very poor outcomes. Although numerous studies have indicated concerns over clinical assessment of degree of dehydration a number of census statements have considered these including European Society for Paediatric Gastroenterology Hepatology and Nutrition (ESPHGAN)
^
21
^ and National Institute for Health Care and Excellence (NICE)
^
22
^ guidelines indicating similar definitions for severe dehydration (with NICE indicating signs of shock to be included). Both review groups recognized that volume of 100 mls/kg for deficit replacement is probably correct for severe dehydration (
^~^10% loss) but the evidence supporting rate of rehydration is very poorly informed with both rapid or ultra-rapid recommendations superseding a previous recommendation of rehydration over a period of 24 hours. NICE guidelines indicated an urgent need for “RCTs to provide cost effectiveness and safety of rapid versus slow rehydration”
^
22
^. 

The overarching aim of GASTROSAM is to generate the relevant evidence for refinement of future guidelines. Potential refinements anticipated include which children benefit from intravenous rehydration, the rate of rehydration and whether children with severe malnutrition should be managed by the same guideline as other children or by a dedicated guideline.

### Our hypotheses

For children with SAM with severe dehydration we hypothesize that the standard intravenous rehydration regime, known as WHO Plan C
^
6
^ (100mls/kg over three to five hours) recommended for non-SAM gastroenteritis with severe dehydration will result in better outcomes than the current very conservative SAM rehydration recommendations. In addition, we propose that the rate of rehydration may be critical and hypothesize that 100mls/kg over eight hours in SAM children could result in fewer fluid related adverse effects than the rapid WHO Plan C guidelines. We also propose that standard ORS solutions may be equally as effective with fewer side effects than lower sodium containing ORS for malnutrition (ReSoMal).

## Objectives

### General objective

To compare the rate and volume of rehydration in children with signs of severe dehydration (see study population) secondary to gastroenteritis on a primary endpoint of 96-hour mortality:

(i) the current standard WHO rehydration protocol Plan C usually used in non-SAM children.

(ii) a slower rehydration regimen using the same total volume (100ml/kg of Ringers Lactate) over eight hours, irrespective of age

(iii) the current WHO restrictive intravenous rehydration strategy for SAM children.

In children with diarrhoea complicated by moderate or ‘some’ dehydration (see study population) and as follow on rehydration post-intravenous rehydration in those with severe dehydration whether oral rehydration with

(i) WHO standard oral rehydration solution (ORS) for non-SAM
^
6
^ is safer and results in less hyponatraemia and better outcomes compared to

(ii) current recommendation advocating low sodium ORS (ReSoMal)
^
5
^

### Specific objectives

(i) To examine survival to 96 hours, Day 7 and Day 28

(ii) Document adverse events, particularly related to cardiovascular compromise and neurological sequelae.

(iii) To examine the feasibility (and adherence to) each of the strategies proposed

(iv) Gather a series of clinical and biochemical data on:

a. Initial assessment of dehydrationb. Response to treatment of children by intravenous rehydration.

(iv) To inform robust definitions of outcomes for a larger phase III trial

## Methods

### Study sites

The trial will be conducted at seven centres in 4 countries; the Mbale Regional Referral Hospital, Uganda, the Soroti Regional Referral Hospital, Uganda, Kilifi County Hospital, Kilifi, Kenya; Coast General Teaching and Referral Hospital, Mombasa Kenya Maiduguri MSF project in Nigeria, Magaria MSF project in Niger, Madarounfa MSF project in Niger.

### Study design

A multicentre open-label Phase II trial of efficacy and safety on survival to 96 hours, seven days and 28 days of rehydration strategies incorporating two strata for management of (A) severe dehydration comparing both rates of rehydration and volume of intravenous fluid replacement and (B) the composition of ORS for children with some dehydration and for children post intravenous rehydration. 

## Study populations

### Inclusion criteria

Children hospitalised with SAM criteria (defined as any of: mid-upper arm circumference (MUAC) <11.5cm, WHZ <-3SD or kwashiorkor)
^
6
^, and aged six months to 12 years, with gastroenteritis (> three loose stools/24 hours):

### Severe dehydration: Stratum A

Signs of severe dehydration (as per WHO definition two or more of: unable to drink; AVPU 2 seconds); or an inability to take or retain oral fluids), with or without shock. Shock will be defined by the recent 2016 WHO emergency triage assessment and treatment criteria; a patient with all of the following: cold peripheries with a weak and fast pulse (rate not specified) and a capillary refill time >3 seconds
^
6
^.

### Moderate/some dehydration: Stratum B

Defined as two or more of the following signs: restlessness or irritable; child is thirsty; child has sunken eyes; or the skin pinch goes back less slowly(<=two seconds).

### Exclusion criteria

Diarrhoea lasting more than 14-days

Known congenital or rheumatic heart disease

Refusal of consent from parents/guardians of patient

## Sampling

### Sample size determination

In versions 1.0 to 2.0 of the GASTROSAM protocol, sample size calculations for the both randomisations were based on studies conducted in children with malnutrition and diarrhoea. For the primary endpoint of urine output for the GASTROSAM A stratum this was based on two African studies have reported on urine output (a surrogate for rehydration and perfusion status) in response to intravenous rehydration. Akech
*et al.* reported persistence of oliguria (urine output <1ml/Kg/hour) at eight hours was more common in those receiving the WHO regimen with hypotonic solution (mean volume 30ml/Kg, with 9/22 (41%) as oliguric) versus children in isotonic Ringers Lactate arm (mean volume 39ml/Kg, 3/25 (12%) as oliguric), p=0.05
^
14
^. In the second study using RL for rehydration oliguria was present in 3/11 (27%) on WHO regime vs 2/9 (22%) standard rehydration fluid-resuscitation
^
15
^.

For Version 3.0 we reviewed the literature on mortality which was informed by an physiological observational study (ARIM) investigating liberal rehydration versus WHO guideline
^
15
^. Overall mortality in the WHO arm was 9/11 (81.8%) to Day 28 and of these deaths 7/11 had occurred by 96-hours (64% mortality). We therefore considered that this was realistic primary endpoint for this current trial of intravenous rehydration strategies and complete retention in the trial to this endpoint (96 hours survivorship) is highly feasible. On the basis of the available data we estimated a slightly lower mortality of 58 % in the WHO arm (as mortality often lower in clinical trials) a 30% relative reduction in mortality rate at 96 hours to 41% in the liberal arm would have a power of 80% and a 2-sided test with alpha 0.05. This would require a higher number in the intravenous rehydration group 270 (or an extra 134 children). The investigator group, including MSF investigators felt that realistic and feasible to enrol ~ 12–15 children per week across 7 sites.

For oral rehydration strategies there have been there have been two studies, both conducted in Asia, examined changes in sodium levels in response to oral rehydration with ReSoMal, with no fatalities in either of the trials
^
18,
19
^. In WHO ORS group, 1/64 (2%) developed severe hyponatraemia (sodium ≤120mmol/L) versus 3/62 (5%) in those receiving ReSoMal. Sodium levels were similar at baseline in both study arms but was lower at 24- and 48-hours in ReSoMal group than the WHO ORS group (p<0.01 and p<0.001 respectively)
^
18
^. A trial comparing ReSoMal versus hypo-osmolar ORS found a greater proportion of children receiving ReSoMal developed hyponatraemia (15.4% vs. 1.9%, p=0.03)
^
19
^.

Based on these data we calculated that for the Stratum A, a randomisation of 270 children would give 80% power (with 1:1:2 randomisation), with 68 to the rapid WHO Plan C arm, 68 to slow rehydration arm (100mls/kg over eight hours), and 135 to the WHO SAM arm to show a 30% lower 96 hour mortality in the liberal strategies compared to WHO SAM arm (control). All children in Stratum A will also be randomised to ORS strategies. In addition including 64 children with some dehydration in Stratum B (1:1) would give 80% power to detect a 3mmol/L difference in sodium levels (assuming mean of 132mmol/L and sd of seven) at 24 hours between the ReSoMal and ORS randomisation (total n=200, 100 per arm (32 some dehydration, 68 severe dehydration)).

Overall, the trial will enrol 334 children across the seven sites.

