Our discussions with the TSC also reconsidered the primary endpoint for the intravenous rehydration strategy which we have changed to mortality at 96 hours. Detailed justification for this is covered in Sample Size Section. It was noted that overall mortality (of the patients recruited into the GASTROSAM Trial to date) is 47%. A mortality which is much lower than previous studies reporting 80% and 65% mortality on children managed on current WHO no rehydration strategy. A concern raised by TSC that if we were to show a significantly better survival for those receiving liberal rehydration would this be sufficient to advocate for guideline change given that mortality is only a secondary endpoint in a Phase II trial? Moreover, if a secondary endpoint demonstrating superior outcome in the liberal rehydration arms were insufficient to change guidelines it would rule out, on ethical grounds, any future trial testing liberal strategies against the current standard of care in children with severe malnutrition. The change in primary endpoint resulted in a recalculation of the sample size and led to a modest increase in Stratum A from sample size of 136 to 270 which has been approved by the TSC and the funders (MRC UKRI).

The outcome of the trial will determine whether the next steps focus on advocacy for a review of the current guideline for rehydration of children with severe malnutrition or whether future trials are needed with sufficient power to show statistical benefits between rehydration strategies for either or both intravenous and/or oral rehydration. 

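### The ORS sample size is still given as 200, from the superseded Stratum A size; the current plan randomises 334 children to ORS, and the stated 80% power matches neither number without an unstated loss

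*Protocol article*

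**What the plan says.** All the relevant figures stand in the protocol article.

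- **Stratum A.** Sample size determination sets it at 270: "a randomisation of 270 children would give 80% power (with 1:1:2 randomisation". The Discussion records that the change of primary endpoint "led to a modest increase in Stratum A from sample size of 136 to 270".
- **Who enters the ORS comparison.** Sample size determination says: "All children in Stratum A will also be randomised to ORS strategies". Treatment allocation says that Stratum A children receive both randomisations at the same time, the oral one in a 1:1 ratio. The section on Stratum A repeats this for all three intravenous strategies.
- **Size and power of the ORS comparison.** The text reads "In addition including 64 children with some dehydration in Stratum B (1:1) would give 80% power" and continues "to detect a 3mmol/L difference in sodium levels (assuming mean of 132mmol/L and sd of seven) at 24 hours". The parenthesis that closes the sentence gives "total n=200, 100 per arm (32 some dehydration, 68 severe dehydration".
- **Total.** "Overall, the trial will enrol 334 children across the seven sites".

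The 24-hour change in sodium is one of the two primary outcomes (Primary outcome).

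**The concern.** One paragraph gives two incompatible sizes for the same comparison. If all 270 Stratum A children and all 64 Stratum B children are randomised to an oral solution, the comparison has 334 children, not 200. The figure of 68 severe children per arm is half of the old Stratum A size, so the sentence appears to have been left unchanged when Stratum A was enlarged.

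This concerns the planned size and power of a primary comparison. A reader who takes the sentence at face value will have the wrong arm sizes and the wrong detectable difference. That reader also cannot judge how much missing 24-hour sodium the comparison can bear. The last point matters here because some children will die before 24 hours, and Table 1 marks 24-hour biochemistry as optional.

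**Working it through.** **Inputs**

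- Difference 3 mmol/L, SD 7, power 80% (Sample size determination).
- Two-sided alpha 0.05. This is stated only for the mortality comparison and is assumed to apply here too.
- Stratum A: formerly 136, now 270. Stratum B: 64. ORS allocation 1:1.
- Unadjusted comparison of two means, normal approximation.

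**Step 1: where 200 comes from**

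- Old Stratum A: 136 + 64 = 200, that is 136/2 + 64/2 = 68 + 32 = 100 per arm. This reproduces the stated total and split exactly.
- Current Stratum A: 270 + 64 = 334, that is 135 + 32 = 167 per arm. This reproduces the stated overall enrolment.
- The step between the two is 270 − 136 = 134, the number of extra children that Sample size determination itself gives.

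**Step 2: number needed for 80% power**

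n per arm = 2 × (7/3)² × (1.96 + 0.8416)² = 85.5, so 86 per arm or 172 in total. An exact t calculation gives 79.8% at 86 per arm and 80.3% at 87, so 172 is right to within a child or two.

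**Step 3: power at each size**

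Power = Φ(3 / (7 × √(2/n)) − 1.96)

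| n per arm | Total | 3 / (7√(2/n)) | Power | t-based power |
|---|---|---|---|---|
| 100 | 200 | 3.03 | 85.8% | 85.4% |
| 167 | 334 | 3.92 | 97.5% | 97.4% |

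The stated 80% is reproduced at neither size. A one-sided 0.05 test does not explain it: at 100 per arm it gives 91.7%.

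**Step 4: difference detectable with 80% power**

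7 × √(2/n) × 2.8016 = 2.77 mmol/L at 100 per arm and 2.15 mmol/L at 167 per arm.

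**Step 5: loss that would bring each size down to 80%**

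- n = 200: 1 − 172/200 = 14%.
- n = 334: 1 − 172/334 = 48.5%.

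**Step 6: power at 334 under a range of overall loss**

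The documents give no 24-hour mortality and no rate of missing samples, so these losses are assumptions, spread equally over the arms.

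| Children without a 24-hour sodium | Power for 3 mmol/L |
|---|---|
| 0% | 97.5% |
| 10% | 96.0% |
| 20% | 93.9% |
| 30% | 90.6% |
| 40% | 85.8% |
| 50% | 79.1% |

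**The case against.** **The 136 could be the two liberal intravenous arms, 68 + 68.** The numbers coincide, but the reading fails. The section on Stratum A applies the oral randomisation to all three intravenous strategies, and the 68 in the ORS sentence is a count per oral arm.

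**The 80% may not be a miscalculation.** This stands. An allowance of about 14% for missing sodium links 172 to 200, and such an allowance may be in the full protocol, which is not shown. A reader might infer that the power was computed wrongly. The article shows only that the 80% is unexplained at n=200 and does not describe the current size.

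**The planned size is not really in doubt.** This stands too. A reader might infer that ORS randomisation could stop at 200. Nothing says so, and the allocation text and the enrolment total settle that it runs to 334.

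**The error is on the safe side.** Agreed. A reader might infer that the ORS comparison is underpowered. On the stated inputs it has more than 80% power unless nearly half of the children lack a 24-hour sodium. The planned regression adjusts for baseline sodium, which would normally raise power above the unadjusted figures.

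**A loss allowance is something an article may leave out.** Its absence is therefore not a separate fault. It matters only because the stated power cannot be interpreted without one. It is also tempting to turn the 96-hour mortality assumptions (58% and 41%) into a 24-hour loss and print one high power figure. The documents do not support that: the time points differ, and full sampling of survivors cannot be assumed when 24-hour biochemistry is optional and Protocol version changes says that some of the Médecins Sans Frontières sites cannot process some samples.

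**Conclusion.** The point holds as an inconsistency in the stated size of a primary comparison. The ORS total of 200 and its split of 68 severe plus 32 some per arm belong to the superseded Stratum A size. The current figures are 334 in total and 167 per arm (135 severe, 32 some). This part rests only on the article's own counts.

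The power statement does not fit the current size either. Without loss, power for 3 mmol/L is about 97.5%, and the difference detectable at 80% is about 2.15 mmol/L. These figures assume SD 7, two-sided alpha 0.05 carried over from the mortality comparison, and no baseline adjustment.

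The error understates the strength of the comparison. It does not threaten enrolment, allocation, the endpoint or the analysis.

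**What to change.** In Sample size determination, replace the ORS total and split with 334 children, 167 per arm (135 severe, 32 some). State the alpha used for this comparison.

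Restate the power for 3 mmol/L, or the difference detectable at 80%, at an evaluable number that the sponsor justifies from expected deaths before 24 hours and from the sites' ability to measure sodium at 24 hours. If no single figure can be defended, give a range such as the one in the last table, and add that about 172 evaluable children give 80% power in the unadjusted comparison.

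If the original 200 included a loss allowance, state it. The cost is a text correction; enrolment does not change.
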